### Randomization

The study participants will be randomly allocated to start with either diet A or diet B. The process will be performed after the first laboratory testing. Randomization will be performed by use of an Internet-based random sequence generator from the School of Computer Science and Statistics, Trinity College, Dublin [http://www.random.org/sequences/]. Due to the small sample size, and to avoid unbalanced allocation of the participants to one of the starting diets, stratified sampling by use of minimization technique will be used. Weighting variables are starting diet and duration of T2DM [28].

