### Design

The ADILAN study is a randomized cross-over open label dietary intervention trial in patients with T2DM who will be instructed to eat two different dietary patterns during two four-week periods separated by a six-week washout period. The procedure for screening, eligibility and recruitment is detailed in Figure 2. Schedule of enrollment, interventions and assessments can be found in Additional file 1. Detailed information about enrollment, interventions and assessments is described in Additional file 2.

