### Data management

Study data will be collected and managed using REDCap™ (Research Electronic Data Capture) electronic data capture tools hosted at Lund University [35]. REDCap™ is a secure, web-based application designed to support data capture for research studies, providing: 1) an intuitive interface for validated data entry; 2) audit trails for tracking data manipulation and export procedures; 3) automated export procedures for seamless data downloads to common statistical packages; and 4) procedures for importing data from external sources.

REDCap™ will be configured according to the study protocol in a way that the researchers can register all data at baseline, 4, 10 and 14 weeks after study start. Only the researchers and the hospital nurses will have access to REDCap™. This web application allows for management of the trial without violation of privacy or participant confidentiality and integrity of allocation concealment. The procedure also facilitates supervision from abroad by some of the investigators.

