### Data analysis

Differences in baseline characteristics between the participants will be measured using two-tailed unpaired *t*-tests. A two-tailed paired *t*-test will be used to analyze treatment effects within subjects and a two-tailed unpaired *t*-test will be used to compare mean values of outcome variables between the two diets. Normal Q-Q plots and Shapiro-Wilk test will be performed to check for normal distribution of data. Data transformation will be applied in case the data does not present normal distribution. To test for a possible period effect a two-tailed unpaired *t*-test comparing the mean difference between first and second period for outcome variables and food intake will be performed. To test a possible carry-over effect a two-tailed unpaired *t*-test comparing the average of observations for outcome variables and food intake between the two periods will be performed. *P* < 0.05 will be considered to indicate statistical significance.

Analysis will be conducted by use of SPSS for Mac Version 20 (IBM SPSS Statistics for Mac, Version 20.0. Armonk, NY: IBM Corp.)

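### The period and carry-over tests do not name the sequence groups, and no consistent reading makes both tests correct

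*Protocol article*

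**What the plan says.** The trial is a two-period cross-over, run "during two four-week periods separated by a six-week washout period" (Design). Under Randomization, "The study participants will be randomly allocated to start with either diet A or diet B". That creates two sequences, AB and BA, and everyone contributes to both periods.

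The Data analysis section then states two checks on the cross-over:

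- Period: "To test for a possible period effect a two-tailed unpaired *t*-test comparing the mean difference between first and second period". The check covers the outcomes and also the dietary intake data.
- Carry-over: a test of the same unpaired, two-sided kind, described as "comparing the average of observations for outcome variables and food intake between the two periods will be performed".

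Neither sentence mentions sequence or starting diet. The section sets a 5% significance level and does not say what follows if either test is significant. Under Data management, the database is set up to "register all data at baseline, 4, 10 and 14 weeks after study start", so values at the start of the second period will exist.

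**The concern.** An unpaired t-test needs two independent groups. In this design those groups are the AB and BA sequences; the two periods hold the same people. Each standard check therefore compares a per-participant summary between sequences: the A minus B difference for a period effect, and the average over both periods for carry-over. The protocol pairs the word unpaired with comparisons between periods, which leaves both tests mis-specified or undefined.

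At stake is what the trial report can say about whether the cross-over worked. These are the only checks of that kind the article states. A period effect could be reported as carry-over or, on another reading, a diet effect as a period effect. The Abstract says the results will be used to judge whether larger studies of similar design are needed, so a wrong statement about carry-over could mislead that judgement.

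**Working it through.** **1. What each contrast estimates.** Write a participant's outcome as subject + period (π1, π2) + diet (τA, τB) + carry-over into period 2 of the diet taken first (λA, λB).

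- AB: P1 = s + π1 + τA; P2 = s + π2 + τB + λA
- BA: P1 = s + π1 + τB; P2 = s + π2 + τA + λB

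Then:

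- P1 − P2, AB minus BA: 2(τA − τB) − (λA − λB). Without carry-over this is twice the **diet** effect; the period terms cancel.
- A − B, AB minus BA: 2(π1 − π2) − (λA + λB). Without carry-over this is twice the **period** effect; the diet terms cancel.
- Participant average, AB minus BA: (λA − λB)/2. This is **differential carry-over**; period and diet cancel.
- All period 1 values against all period 2 values, equal sequences: (π1 − π2) − (λA + λB)/2. This is the period effect mixed with mean carry-over.

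**2. The two consistent readings.**

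| Reading | Carry-over test | Period test |
|---|---|---|
| Literal: period 1 against period 2, unpaired | Wrong: responds to a period effect | Right target, pairing discarded |
| Between sequences supplied in both | Right | Wrong: it is the diet-effect test |

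Neither row is right in both columns.

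**3. Inputs for the size.** The Power calculations section gives 12 subjects for 26 μmol/L fructosamine and 13 for 37 ng/L glucagon, at 80% power and 5% significance. It states no SD, so those numbers cannot be reproduced. Solving backwards with a paired t-test gives SDs of the within-person difference of 29.3 μmol/L and 43.7 ng/L, so the planned glucagon effect is 37/43.7 = 0.85 SD. Assumed here: 13 completers split 7/6, a period shift of 1 SD of the within-person difference (σd), and correlation ρ between periods from 0 to 0.8.

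**4. Why ρ matters.** Each observation has variance σd²/[2(1 − ρ)]. The unpaired comparison of n values per period has standard error √{2 × σd²/[2(1 − ρ)]/n} = σd/√[n(1 − ρ)]. For a 1-SD shift and n = 13, shift over standard error is √[13(1 − ρ)]: 3.61 at ρ = 0, 2.55 at 0.5 and 1.61 at 0.8, against a critical t of about 2.06 on 24 degrees of freedom. For the correct period test the contrast is 2σd and the standard error σd√(1/7 + 1/6) = 0.556σd, a ratio of 3.59 at every ρ.

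**5. Rejection rates by simulation** (at least 20,000 trials per scenario, n = 13):

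| True state | Test | ρ = 0 | ρ = 0.5 | ρ = 0.8 |
|---|---|---|---|---|
| 1-SD period shift, no carry-over | Carry-over test, literal | 93% | 74% | 23% |
| same | Carry-over test, averages between sequences | 5% | 5% | 5% |
| same | Period test, A − B between sequences | 90% | 90% | 90% |
| same | P1 − P2 between sequences | 5% | 5% | 5% |
| Diet effect of 0.85 SD only | P1 − P2 between sequences | 79% | 79% | 79% |
| 1-SD carry-over after one diet | Carry-over test, averages between sequences | 38% | 16% | 9% |

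On the literal reading the period test is the same calculation as the carry-over test, so the first row is also its power for the period shift, to be set against 90%. At ρ = 0 nothing is lost.

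**6. A second scenario.** With 15 participants (8/7), an SD of 29 μmol/L and a 26 μmol/L period effect, the literal carry-over test rejects in 92%, 71% and 20% of trials at ρ = 0, 0.5 and 0.8, and the correct one in about 5%.

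**The case against.** The best defence is that unpaired implies independent groups, that only the sequences qualify, and that the carry-over sentence is a clumsy way of describing each participant's average over both periods compared between sequences. That is a fair parse, and it would make the carry-over test correct. The same parse turns the neighbouring period test into the diet-effect test, so it moves the error without removing it. One could also take the difference in the period sentence to mean A minus B. That quantity spans both periods, however, and cannot be compared between them, so the sentence would still need rewriting.

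Four stronger inferences are tempting and are not supported:

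- *Both harms occur together.* A period effect reported as carry-over needs the literal reading; a diet effect reported as a period effect needs the sequence reading. On one consistent reading only one can arise. On the literal reading a diet effect largely cancels when the sequences are near balance.
- *The primary result is at risk.* No rule drops period 2 or switches the analysis after a significant check, and the paired diet comparison is specified separately.
- *The period test is underpowered in any case.* That holds only on the literal reading and with positive correlation. A cross-over normally counts on such correlation, but the protocol does not state it.
- *Any seasonal difference would trigger the carry-over test.* The primary outcomes are changes within each period, so a constant difference in level cancels. Only a difference between periods in the within-period change would act this way.

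**Conclusion.** The point stands as a mis-specification of two stated diagnostics. Neither sentence names the sequences, and no consistent reading makes both tests correct. On the literal reading, a 1-SD period shift is flagged as carry-over in roughly a quarter to nine-tenths of trials, depending on correlation, where 5% is wanted. On the sequence reading, the period test has no power for a period effect beyond its 5% level and rejects in 79% of trials when there is only a diet effect of planned size.

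The direction of these errors follows from the algebra. Their size rests on assumed values for the correlation, the shift and the split between sequences, none of which the protocol gives. The consequence is a misleading statement about the validity of the cross-over, without bias in the diet comparison. Should-fix.

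**What to change.** Replace the two sentences with:

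> Period effect: A minus B differences compared between the AB and BA sequences by unpaired t-test. Carry-over: each participant's average over both periods compared between the AB and BA sequences by unpaired t-test. Both are reported with 95% CI as descriptive checks, since the carry-over test has low power at this sample size.

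The last clause matters because even the correct carry-over test would detect a 1-SD carry-over in only 9% to 38% of trials, so a non-significant result would not show that carry-over is absent. Optionally, compare the week-10 minus week-0 fasting values between sequences as a direct check of the washout. Those values are already to be collected, and leaving this comparison out is not an error.

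The cost is a change of wording, with no new data, visits or participants.

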## Discussion

As discussed previously, there is uncertainty as to what is the optimal dietary approach for the prevention and treatment of T2DM [11,12,17], and previous trials from our group raise the question of whether focusing on the type of food, rather than macro/micronutrient composition, dietary fiber and GL is a better approach [21,22]. The ADILAN study aims at comparing the effects of two healthy diets on the control of blood glucose, with no significant differences in macro/micronutrient composition, dietary fiber and GL, only different food choice. Importantly, we will try to eliminate weight loss as a confounding factor.

Of paramount importance, the nutritional software package (DIAL) used to create the seven-day menu plan generates a ‘Healthy Alimentation Index’ that classifies both diets as ‘very healthy’. Due to its specific design, constructed on evolutionary principles, the grain/dairy-free diet scored zero in two items, ‘Cereals and legumes’ and ‘Dairy’, but in spite of this, it was classified as very healthy owing to the fact that it scored the maximum (except for ‘Variety of foods with a score of 7/10) in the rest of items’, namely ‘Vegetables’, ‘Fruits’, ‘Meat, Fish and Eggs’, ‘Energy derived from fat’, ‘Energy derived from saturated fats’, ‘Cholesterol’, ‘Dietary sodium’ and ‘Variety of foods’ [32]. It can be concluded that the ADILAN study will compare two healthy diets which are similar in macro/micronutrient composition, fiber intake and GL, for the treatment of T2DM but differing in the intake of cereal grains, legumes and dairy products.

The ADILAN study could serve as a pilot study to run long-term dietary intervention trials in the future, focusing on food choice, which could shed light on a better dietary approach for prevention and treatment of T2DM.

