## Abstract

**Background:**

Research on the role of nutrition in type 2 diabetes has largely focused on macro/micronutrient composition and dietary fiber intake, while fewer studies have tested the effects of differing food choice. Some observational studies and short-term intervention studies suggest that a food pattern mimicking the diet with which humans evolved positively influences glucose control and associated endocrine systems. Such a food pattern mainly differs from other common healthy food patterns in its absence of cereal grains and dairy products. The primary aim of this pilot study is to determine the effect of two healthy diets with or without cereal grains and dairy products on glucose control, while keeping participants’ weight stable and other food parameters, such as macro/micronutrient composition, dietary fiber and glycemic load, the same in both diets.

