#### Healthy diet B

Healthy diet B will include fruit, vegetables, fish, shellfish, lean meat, nuts, eggs and olive oil. Macronutrient composition and fiber intake will not differ from healthy diet A. GL will also be matched to that of healthy diet A. Healthy diet B will exclude cereal grains, legumes and dairy products, which will largely be replaced by root vegetables (including potatoes), vegetables, fruit and lean meat, and slightly more fish and nuts. Healthy diet B is termed ‘healthy diet without cereal grains and dairy products’. Salt intake will be lower in healthy diet B. This diet is also classified as ‘very healthy’ using validated nutritional software package [32]. It is in accordance with official Spanish dietary recommendations for people with T2DM regarding macronutrient composition, dietary fiber, minerals and vitamins (Tables 1 and 2). A detailed description of each of the meals proposed during the course of one week is included in Additional file 3.

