### Dietary design

The main goal of the study is to test the hypothesis that the type of food has an effect on glucose control, independently of macro/micronutrient composition, fiber content, GL and weight loss. Therefore, we generated two different seven-day meal patterns where macro/micronutrient composition and fiber intake are similar. GL is also similar between both seven-day meal patterns. Furthermore, we aim at creating two healthy food patterns, according to official nutritional guidelines in Canary Islands, utilizing a validated nutritional software package (DIAL) [32]. The nutritional composition of the menu plan was analyzed using another validated nutritional software (Dietist XP 3.1; Kost och Näringsdata AB, Bromma, Sweden) to check for possible errors. Minimal differences were observed in the results from both programs. The distribution of macronutrient energy of diets is 19% protein, 28% fat and 53% carbohydrate, and 18% protein, 28% fat, and 53% carbohydrate for healthy diet A and healthy diet B, respectively. The amount of fiber per 2,000 kcal is approximately 48.5 g and 53.1 g in healthy diet A and healthy diet B, respectively. The GL per 2,000 kcal is 116 and 118 in healthy diet A and healthy diet B, respectively. Regarding micronutrient intake, significant differences between the two diets can be seen in Table 2. Importantly, and because one goal of the ADILAN trial is to avoid weight loss, dried fruits were regularly included instead of fresh fruits, in healthy diet B, to match the total weight of food between the two food patterns. Two recent studies have shown that substituting cereal grains for fruits and vegetables increases satiety [19,33], and therefore it may be challenging for the participants to avoid weight loss while adhering to healthy diet B.

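### The stated aim is an effect of food type independent of micronutrients, but the two menus are matched only on energy, macronutrients, fiber and glycemic load; 12 of 19 listed micronutrients differ

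*Protocol article*

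**What the plan says.** Several places state or rely on the diets being matched on micronutrients:

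- Abstract, Background: the primary aim is pursued while keeping weight stable and other parameters, "such as macro/micronutrient composition, dietary fiber and glycemic load, the same in both diets".
- The ADILAN study section: the major aim is an endocrine effect of foods over and above macro- and micronutrient composition, fiber and GL. The working hypothesis sets food choice against those same factors.
- Dietary design: the main goal is to test whether "the type of food has an effect on glucose control, independently of macro/micronutrient composition, fiber content, GL and weight loss". To that end, "we generated two different seven-day meal patterns where macro/micronutrient composition and fiber intake are similar".
- Discussion: the comparison is "with no significant differences in macro/micronutrient composition, dietary fiber and GL, only different food choice". A later concluding sentence again calls the diets alike in micronutrients, and names grains, legumes and dairy as the foods that differ.

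The Dietary design section also says the opposite: "Regarding micronutrient intake, significant differences between the two diets can be seen in Table 2". The Healthy diet B section adds that salt intake will be lower on that diet.

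On the foods removed, the Healthy diet B section states: "Healthy diet B will exclude cereal grains, legumes and dairy products". The title, the aim in the Abstract and the names of both diets mention only cereal grains and dairy products.

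**The concern.** Independence from micronutrients is part of the inference the trial says it wants to draw, so it is more than background description. A cross-over comparison of two menus can support it only if the menus are alike in micronutrients, or if micronutrient intake can be separated from diet in some other way. If the menus differ by design, each participant who follows them changes foods and micronutrients together. A between-diet difference in fructosamine or glucagon then belongs to the whole package.

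The document asserts the matching in its aim and conclusion and denies it in one sentence and one table. An author writing up a positive result from the aim and the Discussion would claim more than the design supports. Because this is a pilot for longer trials focused on food choice, the over-claim could carry into their rationale.

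**Working it through.** **Inputs.** Means, SDs and P-values for the 19 micronutrient rows of Table 2 (calcium to vitamin E). The significance level of 0.05 comes from the Data analysis section and is applied here to Table 2. Legume, dairy and total energy come from Table 1. Assumption: each menu day contributes one value, so n = 7 per diet.

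**Step 1. Count the printed P-values.** Below 0.05: calcium, magnesium, zinc, sodium, potassium, vitamins B1, B2, B6 and C, beta-carotene, vitamins A and E. That is 12 of 19 (63%). Not below: iron, iodine, selenium (0.057), vitamin B3, folic acid, vitamins B12 and D. About 19 × 0.05 = 0.95 rows would be expected by chance. At a Bonferroni level of 0.05/19 = 0.0026, 7 rows remain (calcium, potassium, vitamins B2, B6, C, A and beta-carotene).

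**Step 2. Reproduce the P-values.** Unpaired t-test, t = (mean A − mean B) / [s_p √(2/7)], with s_p² = (SD_A² + SD_B²)/2 and 12 degrees of freedom.

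- Magnesium: s_p² = (70.7² + 49.3²)/2 = 3,714.5, so s_p = 60.9. The standard error is 60.9 × 0.5345 = 32.6 and t = 102.0/32.6 = 3.13, giving P = 0.0087 (printed 0.009).
- Sodium: s_p = 605.3. The standard error is 323.6 and t = 732.6/323.6 = 2.26, giving P = 0.043 (printed 0.042).
- Zinc gives 0.0058 (printed 0.006), selenium 0.058 (0.057) and vitamin E 0.011 (0.01).

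Some do not match: vitamin B1 gives 0.012 (printed 0.004), vitamin C 0.0014 (printed < 0.0001) and vitamin D 0.83 (printed 0.96). None crosses 0.05. The same 12 rows fall below 0.05 with the pooled and the Welch test.

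**Step 3. Size of the differences (B/A, from the Table 2 means).**

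| Micronutrient | Diet A | Diet B | B/A |
|---|---|---|---|
| Potassium (mg) | 3,556.0 | 6,392.9 | 1.80 |
| Sodium (mg) | 1,811.9 | 1,079.3 | 0.60 |
| Calcium (mg) | 978.3 | 591.4 | 0.60 |
| Zinc (mg) | 13.6 | 9.9 | 0.73 |
| Magnesium (mg) | 570.6 | 468.6 | 0.82 |
| Vitamin B1 (mg) | 2.2 | 1.8 | 0.82 |
| Vitamin B2 (mg) | 2.2 | 1.6 | 0.73 |
| Vitamin B6 (mg) | 2.6 | 4.2 | 1.62 |
| Vitamin C (mg) | 170.1 | 434.4 | 2.55 |
| Beta-carotene (μg) | 4,233.7 | 17,194.1 | 4.06 |
| Vitamin A (μg) | 986.3 | 3,021.1 | 3.06 |
| Vitamin E (mg) | 13.0 | 23.7 | 1.82 |

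**Step 4. What does match.** Energy 2,031 against 2,002 kcal (−1.5%), protein 97.2 against 93.0 g (−4.3%), carbohydrate 245.7 against 236.7 g (−3.7%), fat 63.6 against 62.8 g (−1.3%), fiber 48.5 against 53.1 g (+9.5%) and GL 116.1 against 118.0 (+1.6%). The printed P-values for these rows are all 0.2 or above.

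**Step 5. Legumes.** In diet A they supply 185.4/2,031.3 = 9.1% of energy, against 216.6/2,031.3 = 10.7% for dairy. Both are zero in diet B.

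**The case against.** The strongest reply is that nothing is hidden. The Dietary design section points to the micronutrient differences, Table 2 prints every P-value, and lower salt in diet B is announced. On this view, macro/micronutrient is a stock phrase used loosely. Disclosure does stand as a mitigating fact, but it does not reconcile the text: the aim, the main goal and the Discussion still assert what the table denies.

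The P-values compare seven planned menu days per diet, not what participants eat, and four-day weighed food records will measure actual intake. Beta-carotene and vitamin A also overlap, so the 12 rows are not 12 independent findings. This too stands. The sizes in Step 3 are the better evidence, and they are built into the menus. Measured intake is unlikely to separate food choice from micronutrients when the two move together within each of about 15 participants.

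Three stronger readings are tempting and are not supported:

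- **That removing legumes contradicts the claim of differing only in food choice, or defeats the Discussion's conclusion.** Removing legumes is itself a food choice. It is stated under Intervention and Healthy diet B, and the Discussion's concluding sentence names legumes. Only the title, aim and diet names are incomplete.
- **That blood pressure is the main casualty.** Sodium and potassium do differ sharply, but blood pressure is a secondary outcome and lies outside the independence goal, which concerns glucose control.
- **That micronutrients would explain any effect, or that the trial cannot be interpreted.** The documents show no effect of these micronutrients on fructosamine or glucagon, and the effect of one whole diet against the other remains estimable.

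**Conclusion.** The point holds for micronutrients. The statements that the diets are the same, similar or not significantly different in micronutrients conflict with the Dietary design section's own sentence and with Table 2, where 12 of 19 rows differ at P < 0.05 and several differ by 40% or more. The design therefore lacks a property that its main goal requires, and an effect on either primary outcome could not be reported as independent of micronutrients. The claim for energy, macronutrients, fiber and GL is supported.

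This rests on the planned menus being broadly followed. The re-computed P-values also assume seven daily values per diet; the ratios of means do not. The legume issue is a secondary matter of labelling: as worded, the title, aim and diet names invite attribution to grains and dairy alone.

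**What to change.** 1. In the Abstract, the ADILAN study section, Dietary design and the Discussion, restrict the matching claim, aim and hypothesis to energy, macronutrients, fiber and GL. Remove the statements that micronutrients are the same, similar or not significantly different.
2. State in advance that any effect will be interpreted as that of the whole dietary pattern, not as independent of micronutrients. For the secondary blood pressure outcome, name sodium and potassium explicitly.
3. Add legumes to the aim and the diet labels (and to the title where it can still be changed), so that they agree with the Healthy diet B section and the Discussion.

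The cost is wording and a narrower conclusion. Menus, data collection, outcomes, tests and sample size are unaffected.
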